## 4.5 Study measures

### 4.5.1 Exposure

We will identify recorded SARS-CoV-2 infection using data from SGSS, primary care records and SUS. We will include all codes indicative of SARS-CoV-2 infection. SGSS contains the date of an individual's earliest positive SARS-CoV-2 test results from Pillar 1

(NHS and Public Health England laboratories) and Pillar 2 (commercial partners) between 1 February 2020 to the most recent available time point (i.e. the COVID-19 pandemic era).

Individuals meet criteria for inclusion in the COVID-19 exposed group if they:

- Tested positive for SARS-CoV-2 infection in SGSS
- Had a primary care code indicative of SARS-CoV-2 infection
- Discharged from hospital with an International classification of Diseases Version 10 (ICD-10) code in SUS indicative of COVID-19

The index date for those exposed to COVID-19 will be from 28 days after first recording of SARS-CoV-2 infection (i.e., after the earliest date of the record of a positive test in SGSS, primary care coding, or admission in SUS).

Looking at all identified SARS-CoV-2 infections will allow us to investigate how many adverse kidney outcomes can be prevented by preventing SARS-CoV-2 infection altogether through comparisons with people from the general population without known infection. We will also be able to investigate whether outcomes vary based on infection severity (hospitalisation, critical illness, mechanical ventilation and AKI [including requiring RRT]) as well as calendar time and vaccination status through further stratification based on morbidity coding (ICD-10 codes) from SUS. We will categorise people as i) unvaccinated if they had not received any vaccine dose at least 7 days before first recording of SARS-CoV-2 infection, ii) single dose vaccinated if they had received one vaccine dose at least 7 days before first recording of SARS-CoV-2 infection, iii) double vaccinated if they had received two vaccine doses at least 7 days before first recording of SARS-CoV-2 infection, and iv) more than double vaccinated if they had received more than two vaccine doses (including booster doses) at least 7 days before first recording of SARS-CoV-2 infection.

Hospitalised COVID-19 cases will be further investigated through a separate comparison with a historical group. Additional levels of exposure for those hospitalised will include critical care admission, mechanical ventilation, acute KRT and AKI, determined from ICD-10 and procedural codes in SUS.

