### 3. Objectives

Overall, our aim is to investigate long-term kidney outcomes after recorded SARS-CoV-2 infection in the general population.

Our specific objectives are:

1. To describe the relative and absolute rates of ESRD (primary outcome) after recorded SARS-CoV-2 infection compared to both contemporary and historical groups, stratified by:
  - a. Hospitalisation for COVID-19
  - b. Critical care admission for COVID-19
  - c. Mechanical ventilation for COVID-19
  - d. Acute KRT associated with COVID-19
  - e. AKI associated with COVID-19
2. To describe the relative and absolute rates of a 50% reduction in eGFR, incident AKI, and death (secondary outcomes), after recorded SARS-CoV-2 infection compared to both contemporary and historical groups, stratified by:
  - a. Hospitalisation for COVID-19
  - b. Critical care admission for COVID-19
  - c. Mechanical ventilation for COVID-19
  - d. Acute KRT associated with COVID-19
  - e. AKI associated with COVID-19
3. To describe the relative and absolute rates of these outcomes after hospitalisation for COVID-19 compared to a historical hospitalised group, stratified by:
  - a. Critical care admission for COVID-19
  - b. Mechanical ventilation for COVID-19

- c. Acute KRT associated with COVID-19
  - d. AKI associated with COVID-19
- 4. To describe the relative and absolute rates of outcomes after recorded SARS-CoV-2 infection compared to both contemporary and historical groups stratified by:
  - a. Baseline eGFR
  - b. Diabetes
  - c. Age
  - d. Sex
  - e. Ethnicity
  - f. Socioeconomic deprivation
- 5. To describe the relative and absolute rates of outcomes after recorded SARS-CoV-2 infection compared to both contemporary and historical groups additionally stratified by:
  - a. Calendar time
  - b. Vaccination status

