### 4.3 Study designs

We will compare people after SARS-CoV-2 infection to both historical and contemporary cohorts in order to address epidemiological challenges and triangulate meaningful conclusions.

Testing for SARS-CoV-2 during the early stages of the pandemic was restricted due to a lack of infrastructure; therefore many people who were infected (both symptomatic and asymptomatic) will not have been coded as such and so will be misclassified in a contemporary comparison. Using historical comparator groups will allow us to definitively ensure that the comparator group was not infected with SARS-CoV-2 during follow-up. Some comparisons will also be matched on date (i.e., to start follow-up on the same date two years before), which will allow us to account for consistent seasonal variations.

Contemporary comparator populations will account for potential biases we anticipate for any historical comparison. Using a contemporary comparator will also allow us to finely adjust for changes over time during the pandemic (with time since the start of the pandemic as the underlying timescale), such as the emergence of SARS-CoV-2 variants, changes in testing policy, changes in treatment of COVID-19, and differences in ascertainment of outcomes due to reduced access to healthcare (including blood bottle shortages in 2021).

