#### **4.4.5 Follow-up end**

In all analyses we will follow individuals until the earliest of: record of specific kidney outcome under investigation, ESRD, death, no longer registered with GP practice, or study end. Individuals from the matched contemporary comparator group will also be censored at the date of first recorded SARS-CoV-2 infection and will transfer to the exposed group if they survive 28 days after this date.

For analyses using matched historical 2018-2019 comparators, the study end for people with COVID-19 will be the last available date for data at the time of extraction, and for

their matched comparators it will be January 31 2020 at the latest. Our choice of end of follow-up for people with COVID-19 is to be consistent with the available follow-up time for people in the historical comparator group, as we will no longer be able to follow people in the historical comparator group after February 2020 (as we will no longer be sure that those in our comparator group did not have COVID-19 after the start of the initial UK COVID-19 outbreak in February 2020). By allowing the same duration of potentially available follow up for people with and without COVID we will be able to ensure our results are not biased by allowing additional follow up for people with COVID-19 (and consequently allowing more time for them to develop the outcomes under investigation) compared to those without. By allowing the same duration of potentially available follow up for people with and without SARS-CoV-2 infection, we will be able to ensure our results are not biased by allowing additional follow up for people pre-pandemic.

For analyses with the contemporary comparator group, the study end will be the latest available date of fully linked data available on the day the initial cohort is extracted.

[figure not shown]

[figure not shown]

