### **4.6.3 Secondary analyses**

1. We will use Cox regression models to estimate cause-specific hazard ratios and 95% confidence intervals for the secondary outcomes i) 50% reduction in eGFR, ii) AKI and iii) death for individuals after SARS-CoV-2 (stratified as above) compared to individuals in the i) historical and ii) contemporary comparator groups.
2. We will undertake further Cox regression models for both primary and secondary outcomes with SARS-CoV-2 infection stratified by calendar time (i.e. February –

June 2020, July – September 2020, October – November 2020, December 2020 – February 2021, and March – January 2022) and vaccination status.

3. We will fit interaction terms to obtain cause-specific hazard ratio estimates for both primary and secondary outcomes stratified by age group, ethnicity, socioeconomic deprivation, diabetes and baseline eGFR.
4. For people who survive 28 days after hospitalisation for COVID-19, we will undertake an unmatched cohort analysis comparing kidney outcomes with a historical population followed-up from 1 February 2018 restricted to those who survived 28 days after a hospital admission for pneumonia (with or without influenza). This analysis will be stratified by critical care admission, mechanical ventilation, acute KRT and AKI, with additional adjustment for calendar month. The reason for this analysis is to investigate whether COVID-19 is responsible for long-term kidney outcomes to a greater or lesser extent than hospitalisation for other respiratory tract infections.

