|                               |                                                                                                                                                                                                                                                                                                                                                                                                                                                                                                                                                                                                                                                                           |                                                                                                                                                                                                                                                                                                                                                                                                                                                                                                                                                                                                                       | 
therapy (recorded in the 28 days after initial COVID-19 record) from our outcome definition through sensitivity analyses.
 
Instead of calendar time and vaccination status being investigated as additional levels of exposure, we fitted these as interaction terms in secondary analysis to be able to determine stratum-specific effects on individuals with and without COVID-19.
                                                                                                                                                 |

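### The unvaccinated stratum has no calendar limit, so differences between vaccination strata cannot be separated from the era of infection

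*Protocol*

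**What the plan says.** Section 4.5.1 draws positive tests from the surveillance system "between 1 February 2020 to the most recent available time point". It then forms four vaccination levels from doses received at least 7 days before the first record of infection. The lowest level is "unvaccinated if they had not received any vaccine dose at least 7 days before first recording of SARS-CoV-2 infection". No calendar limit is attached to any level.

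Objective 5 in section 3 asks for rates "compared to both contemporary and historical groups additionally stratified by" calendar time (5a) and vaccination status (5b). Section 4.6.3, item 2, plans further Cox models with infection stratified by calendar time, in bands running from February to "June 2020, July – September 2020, October – November 2020, December 2020 – February 2021, and March – January 2022) and vaccination status". Neither place crosses the two factors, adjusts one for the other, or limits the vaccination analysis to the vaccine era.

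Section 4.3 names what changed over the pandemic: variants, "changes in testing policy", treatment of COVID-19, and access to care. Contemporary comparators are matched on the date of the case's infection (4.4.3), with time since the start of the pandemic as the timescale (4.3). For historical comparators, follow-up stops early: for "their matched comparators it will be January 31 2020 at the latest" (4.4.5).

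The deviations table at the end of the protocol (row 4.5.1) reports that, instead of using calendar time and vaccination as exposure levels, "we fitted these as interaction terms in secondary analysis to be able to determine stratum-specific effects on individuals with and without COVID-19". Its row on secondary analyses lists vaccination status and COVID-19 wave among the interactions and describes no joint term.

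**The concern.** Everyone infected before vaccines were available is unvaccinated by necessity. That stratum carries the earliest variants, the most restricted testing and the earliest treatment. The two-dose and more-than-two-dose strata can only come from later periods. Section 4.5.1 sets out to investigate whether outcomes vary by vaccination status, so the strata will be compared with one another.

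A lower HR in vaccinated people could come from vaccination. It could equally come from a milder variant, better treatment, or wider testing that records milder infections. As the analysis is laid out, a reader cannot tell these apart.

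**Working it through.** **Plan's own figure.** The protocol gives no figure for this analysis. Its only calculation, Table 1 in section 5, reproduces: a two-sided 5% comparison of two proportions with 200,000 exposed, five comparators each, 0.02% incidence and HR 1.6 gives 87.5% power against 88% printed. The point below does not depend on it.

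**Step 1: composition of the strata.** The infection window opens on 1 February 2020 (4.5.1). The documents do not give the date of the first vaccine dose; the only assumption needed is that it fell after the window opened. It follows that all pre-vaccine infections are in the unvaccinated stratum and all vaccinated infections are late.

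**Step 2: what date matching removes.** Comparing a case with comparators from the same date removes calendar trends in the background outcome rate from each stratum's HR. Stratifying the Cox model by matched set, as the deviations table reports, likewise absorbs the main effect of date. Neither makes the effect of infection equal across eras. Variant, treatment and testing act on the infected side and can change the HR itself, which is a COVID-19 by era interaction. If that term is absent from the vaccination model, the COVID-19 by vaccination term absorbs it.

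**Step 3: possible size.** Let
- f = pre-vaccine share of the unvaccinated stratum,
- E = ratio of the infection effect, early era to late era,
- v = true ratio of the infection effect, unvaccinated to vaccinated.

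With all vaccinated cases in the late era, and treating the stratum HR as a weighted average over eras, the apparent unvaccinated-to-vaccinated ratio is R = v × (f × E + 1 − f). The documents give none of f, E or v, so the values below are assumed. With no vaccine effect (v = 1):

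| E | f = 0.2 | f = 0.5 | f = 0.8 |
|---|---|---|---|
| 1.0 | 1.00 | 1.00 | 1.00 |
| 1.5 | 1.10 | 1.25 | 1.40 |
| 2.0 | 1.20 | 1.50 | 1.80 |
| 3.0 | 1.40 | 2.00 | 2.60 |

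For example, E = 3 and f = 0.8 gives 0.8 × 3 + 0.2 = 2.60.

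**Step 4: share due to era if vaccination does matter.** The era share of the apparent log ratio is ln(f × E + 1 − f) / ln(R).
- E = 1.2, v = 2, f = 0.2: ln(1.04) / ln(2.08) = 5%.
- E = 2, v = 1.5: 31% at f = 0.2 and 59% at f = 0.8.
- E = 3, v = 1.2, f = 0.8: ln(2.60) / ln(3.12) = 84%.

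**Step 5: effect of restriction.** Dropping infections from before vaccine availability sets f = 0, so R = v. What remains is any difference in era within the vaccine period.

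**The case against.** Objective 5 asks only to describe rates by vaccination status, and the stratified analysis delivers that; the protocol nowhere claims to estimate a vaccine effect. This stands: it would be wrong to say that objective 5b goes unanswered. It does not remove the problem, because the described strata differ in era and invite comparison.

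Calendar time and vaccination appear side by side in section 4.6.3 and in the deviations table, and how they enter a model may be settled in an analysis plan that is not shown. That is fair for the joint term. It does not reach the definition in 4.5.1, which the protocol does fix and which has no date limit. The parallel calendar-time analysis helps a reader see whether HRs vary by era, but not how much of a vaccination contrast is due to era.

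A reader might infer that differences by vaccination status mostly reflect era. The documents do not support this: the era share runs from 5% to 84% on the vaccine effects assumed in step 4, and with E = 1 there is no distortion.

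A reader might also infer that the analysis against historical comparators cannot be estimated, since none of them can be vaccinated. That does not follow. Sections 4.5.1 and 4.6.3 make vaccination a level of the exposure, and the HR of each infected stratum against historical comparators is estimable. The interaction form appears only in the deviations table, which does not say that it was fitted against the historical group and which makes that comparison a sensitivity analysis.

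**Conclusion.** The concern holds in this form: the vaccination strata differ in era of infection by construction, no stated step separates the two, and date matching addresses background trends rather than changes in the effect of infection. Its direction and size are unknown from the documents. With no vaccine effect, the assumed ranges (E from 1.5 to 3, f from 0.2 to 0.8) give an apparent ratio of 1.1 to 2.6. These values illustrate what era alone could produce and are not estimates. The conclusion rests on vaccination having begun after 1 February 2020 and on the infection effect having changed over time; without such a change the strata would be comparable in this respect.

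**What to change.** - Restrict the vaccination-status analysis to infections, and their date-matched contemporary comparators, recorded after vaccine doses first appear in the data.
- Include COVID-19 by calendar band in the same model where event counts allow, so that vaccination strata are compared within a band.
- If vaccination is fitted as an interaction, classify comparators by doses received at least 7 days before their match date. Section 4.5.1 defines status only relative to a first recorded infection, a date that uninfected comparators lack.
- Stratum HRs against historical comparators may stay as description, with a statement that they cannot separate vaccination from era.
- The deviations table reports no data access after 30 June 2024. If re-analysis is not possible, state at least that the vaccination-stratum HRs are not comparable across eras.

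The cost is fewer unvaccinated events and wider intervals. With background incidence assumed at 0.02%, crossing vaccination with band may leave sparse cells. Some era difference also remains within the last calendar band, which is the longest: 11 months if its March start is read as 2021.

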## 4.5.2 Outcomes

### 4.5.2.1 Primary outcome

We will identify incident ESRD through codes for dialysis or kidney transplant using either primary care codes, or ICD-10 or procedural codes from SUS, or eGFR  $<15\text{ml/min/1.73m}^2$  in primary care.

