### 2.1 COVID-19 and AKI

AKI describes a clinical state of potentially reversible reduction in kidney function. It is diagnosed when there is a  $\geq 50\%$  or  $\geq 26.5 \mu\text{mol/L}$  rise in serum creatinine (a biomarker of kidney function) on blood tests compared to baseline, or a reduction in urine output to  $< 0.5 \text{ ml/kg/hour}$  based on body weight. AKI is not unusual in acute illness (due to hypoperfusion and/or inflammatory processes), especially on a background of comorbidity (e.g., diabetes, CKD, heart failure), and factors including increasing age and socioeconomic deprivation also contribute.

Initial reports on the incidence of AKI in COVID-19 from China were low, and this may be because patients had fewer comorbidities and were admitted for less severe COVID-19 than in other settings. A more recent analysis of over 40,000 individuals in the International Severe Acute Respiratory and emerging Infections Consortium World Health Organization Clinical Characterization Protocol UK (ISARIC-WHO CCP-UK) study, a large prospective cohort comprising patients admitted with COVID-19 to over 250 hospitals across the UK up to early December 2020, found that 31.5% of patients developed AKI. As pre-admission serum creatinine data was unavailable, AKI could only be determined in patients who had at least 2 inpatient measurements and so it is possible people more likely to develop AKI were more likely to have repeated tests; conversely, patients with stable

elevated serum creatinine from the time off admission may have been misclassified as not having AKI resulting in underestimation. This study also found that 3% of over 80,000 inpatients required kidney replacement therapy (KRT), the treatment for severe AKI. Pre-existing CKD was strongly associated both AKI and KRT, as were physiological markers of more severe COVID-19 at hospital admission (i.e. tachypnoea and hypoxia). The variability in estimates of the incidence of AKI may reflect differences in national and local criteria for hospital admission as the risk of AKI in mild COVID-19 or asymptomatic SARS-CoV-2 infection remains unknown.

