## 2.2 COVID-19 and CKD

Individuals are primarily diagnosed with CKD when they are found to have an estimated glomerular filtration rate (GFR) (eGFR) persistently  $< 60\text{ml/min/1.73m}^2$  over at least three months. eGFR is usually calculated from serum creatinine, an easily assayed endogenous marker of kidney function but one that is affected by a range of factors related to both its synthesis and excretion such as age, sex, diet, muscle mass, renal tubular secretion, gut loss, muscle catabolism and genetic ancestry. CKD can also be diagnosed by urinary albumin creatinine ratio  $>3\text{ mg/mmol}$  or in the presence of a structural kidney abnormality (e.g. polycystic kidneys or dysplastic kidneys).

Trajectories of eGFR can vary and progressive decline to  $<15\text{ ml/min/1.73m}^2$  results in end-stage renal disease (ESRD) (also known as “kidney failure”) with long-term KRT required to sustain life (in the form of dialysis or kidney transplantation). In addition to ESRD, CKD is associated with increased all-cause mortality, cardiovascular mortality and morbidity, and AKI. Complications of CKD include anaemia, hyperkalaemia, hypervolaemia, altered pharmacokinetics, and secondary hyperparathyroidism^7. CKD is common, affecting 8.5% of the UK population, and is associated with a substantial burden on healthcare costs.

AKI is a risk factor for CKD. After SARS-CoV-2 infection, tubular injury, de novo immune-mediated processes (such as collapsing glomerulopathy), or direct infection of kidney parenchyma might independently cause additional insults leading to long-term kidney

disease. In addition, pre-existing CKD is an independent risk factor for severe outcomes in COVID-19, plausibly leading to accelerated renal decline in those most at risk.

Given the scale of COVID-19 hospitalisation, including COVID-19-related-AKI, there is a pressing need to understand whether this will lead to an increased burden of CKD and its complications on health systems, given the potential stresses on resources that these will incur.

There has been a gradual increase in the number of studies focusing on post-COVID-19 complications, and some of these include the incidence or progression of kidney diseases.

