### 4.4.1 Exposure group

Our exposure group will comprise people with recorded SARS-CoV-2 infection identified using data from SGSS, primary care records or SUS who remain alive 28 days after the first recording of infection (i.e. 28 days after date of testing positive in SGSS, coding in primary care records, or admission on SUS) (index date) (Figure 1).

Anyone coded in primary care or SUS to be receiving chronic dialysis or kidney transplant or with  $\text{eGFR} < 15 \text{ ml/min/1.73m}^2$  (i.e. anyone with ESRD or CKD Stage 5) at the time of first recording of SARS-CoV-2 infection will be excluded.

A secondary analysis will investigate individuals who remain alive 28 days after the date of first hospital admission coded for COVID-19 in SUS. Anyone coded in primary care or SUS to be receiving chronic dialysis or kidney transplant or with  $\text{eGFR} < 15 \text{ ml/min/1.73m}^2$  (i.e. anyone with ESRD or CKD Stage 5) at the time of hospital admission will be excluded.

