### 4.5.2.2 Secondary outcomes

1. 50% reduction in eGFR

This analysis will exclude anyone without a baseline eGFR measurement. We will be cautious when interpreting our analysis of eGFR outcomes as this is unlikely to be generalisable to the general population and only to people who had an indication for baseline eGFR testing (e.g. comorbidities, drugs).

Baseline eGFR will be defined as the mean primary care eGFR calculated from serum creatinine using the CKD-EPI equation from 18 months before the index date up to 14 days before the index date (or 14 days before hospital admission date for hospitalised COVID-19 cases).

Primary care eGFR measurements will be followed-up monthly from the index date, until criteria for the outcome endpoint is met (50% reduction in eGFR from the baseline eGFR).

The OpenSAFELY platform is currently only able to extract a predefined number of measures for any variable (i.e., it is not possible to extract all available measures); we will therefore extract and use the last eGFR measure for every calendar month in follow-up.

Incident ESRD (i.e. dialysis or kidney transplant primary care codes, or ICD-10 or procedural codes from SUS, or eGFR  $<15\text{ml/min/1.73m}^2$  in primary care) will also be included in the outcome definition.

We will also consider assessing changes in eGFR trajectory using slopes.

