#### **4.6.4 Sensitivity analyses**

We aim to investigate the robustness of our primary and secondary analyses by exploring assumptions further using a range of sensitivity analyses, including:

1. Competing risk analysis

Due to the competing risk of death, we will undertake a competing risk analysis using Fine and Gray regression models to obtain subdistribution hazard ratios for ESRD.

2. Multiple imputation for ethnicity

In our main analyses, we will undertake a complete case analysis for ethnicity (i.e. only include individuals with recorded ethnicity data). In this sensitivity analysis, we will use multiple imputation for missing ethnicity data.

3. Complete case analysis for smoking and BMI

In our main analysis, we will assume that individuals without smoking status are non-smokers and that individuals without BMI have normal BMI. In separate sensitivity analyses, we will instead undertake complete case analyses (i.e. only including individuals with complete smoking and BMI data respectively).

4. ESRD definition

In case of possible residual misclassification of AKI as ESRD (where an individual has an eGFR  $<15\text{ml/min/1.73m}^2$ ), we will undertake a sensitivity analysis restricting only to people with new codes for dialysis or transplantation (i.e., incident KRT).

5. Incident eGFR  $<30\text{ml/min/1.73m}^2$

As healthcare services have been impacted heavily by the pandemic, there may not have been sufficient routine testing of patients to be able to detect a reduction in eGFR. As patients who are highest risk may be prioritised, we will also investigate for incident eGFR  $<30\text{ml/min/1.73m}^2$  in primary care or new codes for dialysis or kidney transplant in either primary care records, or ICD-10 or procedural codes from SUS.

6. eGFR equation

In our main analyses, we will calculate eGFR using the CKD-EPI equation from 2009 (without adjusting for ethnicity). This equation has recently been updated excluding adjustment for ethnicity. We will assess how many individuals change CKD stage from the original CKD-EPI equation after switching to the 2021 equation. If there are marked differences in the number of people with CKD and within each CKD stage, we will undertake a sensitivity analysis using the 2021 equation instead for eGFR.

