| 
4.5.1 Exposure
                                                                | 
We will also be able to investigate whether outcomes vary based on infection severity (hospitalisation, critical illness, mechanical ventilation and acute kidney injury [including requiring renal replacement therapy]) as well as calendar time and vaccination status...
                                                                                                                                                                       | 
We did not use mechanical ventilation or renal replacement therapy as additional levels of exposure.
                                                                             | 
We decided there would be little added benefit in disaggregating mechanical ventilation from critical care admissions, especially in the context of heightened competing risk of death.
 
We did not include acute renal replacement therapy as an additional level of exposure as it was included in our outcome definition (we defined kidney failure as incident dialysis [including any acute renal replacement therapy records recorded between initial COVID-19 record and index date 28 days later on day 1 of follow up], kidney transplantation, or estimated glomerular filtration rate <15ml/min/1.73m^2). However, we investigated the effect of including and excluding acute renal replacement
 |

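### The primary ESRD outcome does not separate acute from chronic dialysis, and the planned sensitivity analysis on its definition does not test this

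*Protocol*

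**What the plan says.** The primary outcome (Protocol 4.5.2.1) has two routes. The code route reads: "We will identify incident ESRD through codes for dialysis or kidney transplant using either primary care codes, or ICD-10 or procedural codes from SUS". The second route is a primary-care eGFR below 15. Neither carries a minimum duration or a confirmatory record.

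Elsewhere the protocol uses a narrower idea. Section 2.2 describes ESRD as the end of progressive decline, "with long-term KRT required to sustain life". The baseline exclusion in section 4.4.1 removes "Anyone coded in primary care or SUS to be receiving chronic dialysis or kidney transplant", or with eGFR below 15; sections 4.4.2 and 4.4.3 apply the same exclusion to comparators.

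Section 4.6.4, item 4, is the planned check on the definition. It opens "In case of possible residual misclassification of AKI as ESRD (where an individual has an eGFR" below 15, and the remedy is "restricting only to people with new codes for dialysis or transplantation (i.e., incident KRT".

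The deviations table (row for 4.5.1 Exposure) gives the outcome as used. Incident dialysis counted, "including any acute renal replacement therapy records recorded between initial COVID-19 record and index date 28 days later on day 1 of follow up". The same row says that acute RRT was dropped as an exposure level because it was part of the outcome. It adds that sensitivity analyses were run with and without acute RRT from those 28 days.

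**The concern.** The protocol separates acute from chronic dialysis when it excludes people at baseline and when it forms exposure strata, but not when it counts primary events. The exclusion applies at first recording of infection, so someone who starts acute dialysis for COVID-19 AKI after that date stays in the cohort. If dialysis is still being coded after day 28, or is coded for a later AKI, the person becomes an incident ESRD case even if kidney function then recovers.

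Acute dialysis is plausibly commoner among people who had severe COVID-19 than among general-population comparators, so the likely direction is upward in the hospitalised, critical-care and AKI strata. The study asks about long-term kidney outcomes, and an acute effect could be read as a chronic one. The definition also spreads: ESRD is part of the 50% eGFR-reduction outcome (4.5.2.2) and ends follow-up in every analysis (4.4.5).

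**Working it through.** **Step 1. Compare the definitions.**

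| Place in the Protocol | Dialysis that qualifies | Persistence required |
|---|---|---|
| 2.2, concept of ESRD | long-term KRT | yes, by meaning |
| 4.4.1 to 4.4.3, exclusion | chronic dialysis | yes, by wording |
| 4.5.2.1, primary outcome | any dialysis code | none |
| 4.6.4 item 4, sensitivity | any new dialysis code | none |
| Deviations table, 4.5.1 row | incident dialysis, plus acute RRT on days 0-28 | none |

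Item 4 names the right error, AKI read as ESRD, but locates it only in the eGFR route. Removing that route leaves every acute dialysis code in place.

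The eGFR route is also unconfirmed. For the eGFR-reduction outcome section 4.5.2.2 says "we will therefore extract and use the last eGFR measure for every calendar month in follow-up", but no second value below 15 is required.

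**Step 2. Reproduce the plan's own figure.** Inputs from section 5: 200,000 exposed, incidence 0.02%, hazard ratio 1.6, 5% level (taken as two-sided). Sections 4.4.2 and 4.4.3 give five comparators per exposed person. A two-proportion test with pooled variance under the null gives:

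- expected events: 200,000 × 0.0002 × 1.6 = 64 exposed, 1,000,000 × 0.0002 = 200 comparators
- pooled proportion: 264 / 1,200,000 = 0.00022
- null SE: √(0.00022 × (1/200,000 + 1/1,000,000)) = 0.0000363
- alternative SE: √(0.00032/200,000 + 0.0002/1,000,000) = 0.0000424
- z = (0.00012 − 1.96 × 0.0000363) / 0.0000424 = 1.15, so power is 87.5%

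Table 1 states 88%. The power table is sound and is not part of this point.

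**Step 3. Illustrate the scale.** With no true effect, expected exposed events are E = 200,000 × 0.0002 = 40. If *a* acute-dialysis events are added to the exposed only, the apparent ratio is (E + *a*) / E.

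- ratio 1.6: *a* = 0.6 × 40 = 24; check (40 + 24) / 40 = 1.6
- ratio 2.96, the hazard ratio cited in section 5: *a* = 1.96 × 40 = 78.4, about 78

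To relate this to acute KRT, section 2.1 reports that "3% of over 80,000 inpatients required kidney replacement therapy (KRT". Applying 3% to 200,000 survivors gives 6,000 people. This is an assumption, since the cited figure is for all inpatients, including those who died. A lower assumption of 1% gives 2,000.

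| Background incidence | E | *a* for ratio 1.6 | Share of 6,000 | Share of 2,000 |
|---|---|---|---|---|
| 0.02% (plan) | 40 | 24 | 0.4% | 1.2% |
| 0.10% (five times, assumption) | 200 | 120 | 2.0% | 6.0% |

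**Step 4. Let comparators have acute dialysis too.** If the same definition adds *c* events per 200,000 comparators, the ratio is (40 + *a*) / (40 + *c*), and 1.6 requires *a* = 24 + 1.6*c*. With *c* = 10 (assumption), *a* = 40; check 80 / 50 = 1.6.

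**The case against.** Several points on the other side stand.

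- **Follow-up starts at day 28.** A reader might infer that the primary hazard ratio would mainly measure dialysis during the index illness. The documents do not support that. Under the plan, dialysis coded only on days 0-28 is not an event, and no figure is given for the share still dialysed, or newly dialysed, after day 28.
- **The later sensitivity analyses help.** The deviations table reports results with and without acute RRT from days 0-28, which deals with that window. It does not deal with acute dialysis after day 28.
- **Comparators have a matching window.** A reader might infer that the day-1 rule could apply only to the exposed. Comparators are matched on date (4.4.2, 4.4.3) and, per Figure 1, followed from 28 days after matching. The table does not say whether the rule was applied to them; silence does not prove asymmetry.
- **The acute-KRT stratum is not identical to the outcome.** The stratum looks back from index (4.4.4), outcomes count forward, and the stratum was later dropped because of the overlap.
- **The eGFR route is partly protected.** It uses primary-care results only, and item 4 removes it.
- **The code lists are not shown.** They are archived online (4.7) and might separate chronic from acute codes. The protocol text does not say so, and the deviations table says that acute RRT was in the outcome.
- **The illustration is favourable to the concern.** It uses a general-population incidence and, in Step 3, adds events only to the exposed. Five times the background, or acute dialysis in comparators, raises the number needed.

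None of this supplies the missing distinction or a planned analysis that tests it.

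**Conclusion.** The concern holds for the dialysis route after day 28. The outcome definition is wider than the protocol's own concept of ESRD and its own exclusion, and the safeguard written for this error does not reach it. The deviations table confirms that acute RRT was in the outcome and extends it to days 0-28, a window that its added sensitivity analyses do cover.

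The size of the bias cannot be derived from the documents. With an outcome as rare as 0.02%, few misclassified events matter: 24 among 200,000 exposed on the plan's incidence, 120 at five times that incidence, and more if comparators also contribute. These figures show sensitivity and do not estimate bias. They rest on no true effect and on the assumed shares of survivors with acute KRT. The supported statement is that the hazard ratio in the severe strata could be inflated.

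**What to change.** - **Primary outcome.** Align the dialysis route with the exclusion: chronic-dialysis, ESRD or transplant codes, or dialysis still coded about 90 days after the first dialysis code. Ninety days agrees with the three-month standard that section 2.2 uses for CKD.
- **Event date and death.** Date the event at the first qualifying code, and say where it is placed if that code precedes index. A persistence rule conditions on survival, so state how death or end of data before confirmation is handled.
- **Section 4.6.4, item 4.** Replace or extend it with an analysis that excludes acute or unconfirmed dialysis codes as well as unconfirmed eGFR below 15.
- **Any KRT including acute.** Report this as a sensitivity analysis, and state that the same 28-day rule applies to comparators.

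The cost is a change to code lists and derivation if the data are still available. Whether a separate chronic-dialysis list exists cannot be verified from the documents; the persistence rule is the alternative if it does not. Late events, and events followed by early death, cannot be confirmed, so both versions should be shown.

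The deviations table (row for 4.6.2) reports no data access after 30 June 2024. If re-derivation is impossible, relabel the outcome as including acute KRT and give the result without day 0-28 acute RRT equal prominence.
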